## 6.2 Eligibility Criteria

There have been a number of considerations in establishing the eligibility criteria and thus the recruitment strategy for the right@home trial. These include:

1. Longitudinal research about antenatal predictors of maternal and child outcomes. One of the key findings from CCCH's first literature review (**Appendix 3**) was that home visiting programs are more effective for families of low socioeconomic backgrounds. However, SNHV trials typically recruit based on a small number of risk factors (e.g. teenage parent, poverty). As such, it is not possible to say whether women with other known risk factors for poorer child development and learning outcomes may benefit from SNHV programs. For example, Chittleborough et al (2012) found that antenatal maternal factors such as teenage parent, single parent, low education, perinatal depression, poverty and smoking were strongest predictors of poor parent-infant related outcomes. PREview (<http://www.chimat.org.uk/preview/evidence>) indicates that postnatal (child 9 months) maternal predictors of child health, learning and behavioural outcomes at age 5 years were low income, low education, poor general health and low self efficacy. Following from this, we selected the risk factors to be tested by the recruitment pilot to encompass a range of socioeconomic and psychosocial characteristics.

2. Important "success" factors in previous SHNV trials relate to cohort "vulnerability". Summaries of the SNHV literature point to the added value of these programs for more vulnerable families, particularly those with low psychological resources and supports. Research reviews have also recognised that, while the most vulnerable might be those most likely to benefit, they are also hardest to recruit and retain in studies. Risk factors cluster together and, for the purposes of the right@home trial, we are assuming that the greater number of risk factors a woman has, the more 'vulnerable' she is.

3. Risk factors of the MECSH population. These included maternal age under 19 years, EPDS score  $\geq 10$ , lack of emotional and practical support, late antenatal care, major stressors in the past 12 months, current substance misuse, current/history of mental health, history of abuse in mother's childhood and domestic violence. As the right@home trial builds off MECSH, we incorporated these risk factors into the pilot screening survey, to assess whether they were useful markers of vulnerability.

4. Pilot study to inform right@home eligibility criteria and recruitment procedure.

### Background

For the right@home pilot recruitment study, we hypothesised that a screening survey delivered in antenatal waiting rooms – with questions targeted at maternal risk factors, particularly those known to be important for future child health – would capture vulnerable women likely to benefit from the right@home SNHV intervention. The screening survey items included age (calculated from year of birth), relationship status, social support, general health, having a long-standing illness, anxious mood, education level, current employment, and proxy measures for poverty (whether the woman receives Centrelink benefits and/or owns a healthcare card (HCC)).

To test this hypothesis, we linked the screening survey data with midwifery-collected data recorded on the hospital's electronic Birthing Outcome System (BOS), which includes more sensitive risk factors (i.e. those that can be more difficult for women to feel comfortable disclosing in a public waiting room). These variables included smoking during pregnancy, alcohol use, drug use, marijuana use, social issues, domestic violence, a history of mental health problems, and an EPDS score.

## Results

*Sample characteristics:* The 3-day pilot study was conducted at Northern Hospital, Epping. Of 118 women approached, 102 (86.4%) took part. The survey data were near-complete (few missing data) and, when asked, women did not express concern with the survey questions, suggesting that the survey was acceptable to women and feasible to collect in busy antenatal clinic waiting rooms. Women ranged in age from 18-41 years. The length of women's pregnancies ranged from 0-40 weeks, skewed towards the later months (median 32 weeks; interquartile range 24, 35 weeks).

81/102 women (79%) consented to having their screening survey data linked with their midwife-collected BOS data. The number and proportion of women with each risk factor is listed in Table 3 below. We excluded the Centrelink, HCC, and current employment risk factors from the agreement analysis (described below) because they did not differentiate risk in the sample, i.e. large proportions of the sample responded positively to the items. After these, the most common waiting room risk factors were young pregnancy (<23 years), poor/fair/good general health, not finishing high school and no previous employment.

*Agreement between screening survey and BOS data:* Of the 81 women with complete data, 21 had any 1 or more BOS risk factors (proportions also presented in Table 3 below). Of these, 6 were current smokers only with no other BOS risk factors, and 3 were current smokers with at least one other BOS risk factor. Six women had BOS risk factors but no waiting room risk factors and, of these, four had the single BOS smoking risk factor and no others. This means that if we add smoking status to the waiting room screening survey items, we would only miss only two women with BOS risk factors (2/21, 9.5%) of the participating waiting room population.

Our research team, including CI [name] (statistician), examined different algorithms for identifying which eligibility criteria would identify the most vulnerable women. These analyses demonstrated that choosing women based on 2 or more of the following 10 screening survey risk factors would sufficiently identify vulnerability: current smoking, young pregnancy (<23 years old), no support during pregnancy, poor/fair/good general health, anxious mood, not finishing high school, not having a household income, long-term illness, living without another adult, and not working previously. For example, of the 21 with a BOS risk factor, 12 (57%) were captured with 2 or more of the above risk factors. Of the 81 participants with complete data, 24 were captured (30%) and, of the total sample screened, 32/102 (31%) were captured.

We therefore intend to use these ten risk factors to screen women for the main right@home trial. However, an overall eligibility rate of 30% is high and may mean that some eligible women are not sufficiently vulnerable to benefit from the SNHV program. To identify these women, we will reassess their vulnerability based on the comprehensive demographic information we collect at the baseline assessment, for the first 20 women enrolled. This will help us refine our eligibility criteria if necessary. In addition, as less-vulnerable women tend to self-select out of intensive parenting

programs (e.g. as in the MESCH trial), women and their nurses will be asked if they think they need the program. If both the woman and her nurse do not think the woman needs the program, the team will consider excluding the woman and refining the eligibility criteria. This will help prevent excessive attrition and protect study power.

**Table 3:** Proportions of participants with screening survey and BOS risk factors

| Risk Factor                     | Sample, n (%)         |                             |
|---------------------------------|-----------------------|-----------------------------|
|                                 | Complete data
N=81 | ≥ 1 BOS risk factor
N=21 |
| Screening survey         |                       |                             |
| <23 years old                   | 10 (12.4)             | 2 (9.5)                     |
| No support                      | 4 (4.9)               | 2 (9.5)                     |
| Poor/fair/good health           | 24 (29.6)             | 10 (47.6)                   |
| Anxious mood                    | 5 (6.7)               | 3 (14.3)                    |
| <Year 12 education              | 19 (23.5)             | 9 (42.9)                    |
| No household income             | 5 (6.7)               | 4 (19.1)                    |
| Long-term illness               | 3 (3.7)               | 0                           |
| Living without adult            | 1 (1.2)               | 1 (4.8)                     |
| No previous work                | 10 (12.4)             | 1 (4.8)                     |
| No current employment           | 52 (64.2)             | 16 (76.2)                   |
| Centrelink benefits             | 37 (45.7)             | 15 (71.4)                   |
| HCC                             | 32 (39.5)             | 11 (52.4)                   |
| BOS items                |                       |                             |
| Current smoking                 | 9 (11.1)              | 9 (42.9)                    |
| Alcohol use                     | 3 (3.7)               | 3 (14.3)                    |
| Drug use                        | 1 (1.2)               | 1 (4.8)                     |
| Marijuana use                   | 2 (2.5)               | 2 (9.5)                     |
| Social issues                   | 3 (3.7)               | 3 (14.3)                    |
| Domestic violence               | 1 (1.2)               | 1 (4.8)                     |
| History of mental health issues | 8 (9.9)               | 8 (38.1)                    |
| EPDS >12                        | 1 (2.1)               | 1 (8.3)                     |

Participants will be assigned to a randomised study treatment only if they meet all of the inclusion criteria and none of the exclusion criteria.

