- b) Postnatal Learning to Communicate program consisting of 12 monthly sessions commencing when the baby is one month old and finishing when the baby is 12 months old, which include information and activities for parents to encourage child development. Sessions 1-5 are delivered individually during the home visits. Sessions 6-12 are delivered in a group environment. The effectiveness of the Learning to Communicate program has been demonstrated in an unpublished controlled trial, and is a published clinical resource used by clinicians throughout Australasia.

- c) Access to early childhood health services, volunteer home visiting services and family support services.
- d) Group activities and community links including parenting group and walking group specifically for intervention families, and linking into community activities.

The intervention incorporates the standard Key Age and Stage (KAS) visits described in the Service Design Concept above. Existing MECOSH nurse visit checklists (see examples in Manual in **Appendix 5**) will be modified to include statements regarding the need to do KAS at the appropriate times.

**Usual care (control) group:** The control group receive the usual care; that is:

- a) Antenatal care according to MCH protocols, which include:
  - One postnatal home visit by a nurse from the regular child and family nursing service (within 2 weeks of baby's birth)
  - Additional postnatal home or clinic visits with the regular child and family nursing service as indicated by protocols in usual care.
- b) Volunteer home visiting services and family support services within the postcode area as available

Being in the right@home study (both control & intervention) will not preclude access to other support services, except for being part of the Cradle to Kinder (CtK) programs (see Exclusion Criteria, Section 6.2).

Hence the key differences between the right@home intervention and usual care are:

- Home visiting commencing antenatally;
- Continuity of care by the same nurse throughout the 2½ year program;
- Care by nurses with additional training in the right@home and MECOSH program model;
- Standardised postnatal home visiting program to the child's second birthday;
- More frequent, sustained and responsive visits in right@home
- Dedicated social care practitioner;
- Learning to Communicate program and specialised toolkit of focus modules;
- Group activities and proactive links to community activities.

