### **6.2.2 Exclusion Criteria**

Women will be excluded if:

- Their child is removed from the home during the course of the research such that they are ineligible for the trial. If it emerges that child is being removed from his/her home (i.e. intervention nurses inform the study team, or a researcher phone call to the mother to schedule an assessment reveals it), then the CIs [name] and [name] will consider whether the family can remain in the trial on a case-by-case basis. Remaining in the trial will depend on the length of time the child is removed from the home, as it is not possible to assess the effectiveness of an intervention if the family has no access to the intervention or usual care alternative. In some cases, it will only be possible to consider full exclusion of a family at the end of the trial.
- They are enrolled in the Victorian Department of Human Services 'Cradle to Kinder' research program
- They are enrolled in the Tasmanian Department of Health and Human Services CU@home home visiting program
- Do not comprehend the recruitment invitation (e.g. have an intellectual disability such that they are unable to consent to entering the study, or have insufficient English to complete face-to-face assessments, i.e. require an interpreter)
- Have no mechanism for contact (landline or mobile telephone, or email address)
- Experience a critical event such as miscarriage, late termination of pregnancy, stillbirth and neonatal death.

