#### **6.6 Subject Withdrawal**

##### **6.6.1 Reasons for withdrawal**

The research team may withdraw a participant from the study treatment and follow-up procedures if the participant:

- Is in violation of the protocol
- Experiences a serious or intolerable adverse event
- Develops, during the course of the study, symptoms or conditions listed in the exclusion criteria
- Requires early discontinuation for any reason
- Experiences a critical event such as miscarriage, late termination of pregnancy, stillbirth and neonatal death.

The latter will be identified via the research phone calls made throughout the study. We understand that it may be extremely difficult for women to share this information, so phone calls will be

conducted using the same sensitive procedure employed in other studies conducted at the MCRI. The researcher will begin the conversation by asking the mother how she is, which allows the mother to volunteer the information. For mothers in the intervention arm, intervention nurses are likely to learn of these events before the researcher. Intervention nurses will then pass this information back to the research CIs, and one of the CIs will contact the parent to express their sadness, take them off the database, and offer the maternal and child health service number in case parents want additional support. For control participants, the researcher conducting the phone call (CI [name] or RO [name]) will offer the same information, and ask whether the mother would like CI [name] to contact their maternal and child health nurse to request more support.

At enrolment, women will be given study details on the PIS&C, and invited to contact the study team with any details they think we should know about. These processes have worked well in other MCRI studies.

The research team will withdraw all participants from the study treatment if the study is terminated. Patients are free to withdraw from the study at any time upon their request or the request of their legally acceptable representative.

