## **7. STUDY VISITS AND PROCEDURES SCHEDULE**

The Study diagram in Section 4.2 and Figure 3 below depict the study visits schedule. From April 2013 to March 2014, researchers will approach women at antenatal clinics listed in Section 1.1 to invite women to take part in the screening survey (**Appendix 15**). At this point, consent involves agreeing to complete the screening survey and, if eligible, being invited into the right@home trial. Researchers will then visit interested and eligible women in their homes within 1-2 weeks of the initial screening procedure, to tell them more about the right@home study, and collect informed consent for participation in the randomised controlled trial and a thorough baseline assessment.

Once women complete the baseline assessment, they will be randomised into one of the intervention or usual care arms. Whether this randomisation takes place in the woman's home (at the end of the enrolment visit) or over the phone will depend on whether the intended electronic data collection processes can incorporate the web-based randomisation program, and whether the tablets can connect via 3G/wireless internet. Once a woman is randomised, her details will be sent to the right@home nurse coordinator responsible for that region, and the nurse will be responsible for initiating contact and beginning the intervention. Follow-up assessments will be conducted by the research team via phone at 6 weeks, 6 months and 18 months postpartum, and via face-to-face home visits at 12 and (the final follow-up at) 24 months.

Due to the anticipated low literacy level of the participant group, we are designing all assessments so that they can be completed face-to-face by interview. Responses will be recorded by researchers electronically on tablets, except for some sensitive questions (highlighted in the questionnaire), where the participant will be given the option to complete by themselves either by reading it or having it read to them.

**Figure 5: Graphical depiction ('Perera diagram') of the components of the trial shared and unique to the intervention and control groups**

| Time point relative to randomisation                | Intervention                                                                                                             | Control |

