## **10.2 Population to be analysed**

The intention-to-treat population will be used in the analyses. Mothers (and children) will be compared according to the group to which they were randomly allocated, regardless of mothers' compliance, crossover to other treatments or withdrawal from the study. This approach preserves the prognostic balance in the study arms achieved by randomisation.

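### Two rules let randomised women be excluded after allocation (program judged not needed; child removed from the home), which conflicts with the as-randomised analysis and can bias the comparison

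*Protocol*

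**What the plan says.** Four places in the protocol bear on who stays in the comparison.

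- **Section 6.2, pilot results.** Women and their nurses are to be asked whether the program is needed. "If both the woman and her nurse do not think the woman needs the program, the team will consider excluding the woman", and the eligibility criteria may be refined. The stated purpose is: "This will help prevent excessive attrition and protect study power". No time point, arm or limit is given.
- **Section 6.2.2.** One exclusion criterion reads: "Their child is removed from the home during the course of the research such that they are ineligible for the trial". Named investigators decide case by case. They may learn of a removal from intervention nurses or from a research phone call. "In some cases, it will only be possible to consider full exclusion of a family at the end of the trial".
- **Section 6.6.1.** "The research team may withdraw a participant from the study treatment and follow-up procedures if the participant" meets one of the listed conditions, which include developing an exclusion condition while on study.
- **Section 10.2.** "Mothers (and children) will be compared according to the group to which they were randomly allocated", whatever their compliance, crossover or withdrawal.

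Two further statements settle the likely timing. Section 7 says: "Once a woman is randomised, her details will be sent to the right@home nurse coordinator responsible for that region". For usual care, the first nurse contact listed in Section 5.1.1 is: "One postnatal home visit by a nurse from the regular child and family nursing service".

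**The concern.** An exclusion made after randomisation protects the comparison only if it is unrelated to both arm and prognosis. Neither rule meets that test.

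The need-based rule depends on a nurse's view of whether a woman needs the program. That view is naturally available where the program is being delivered, and it picks out women thought less vulnerable. Removing them from the intervention arm while their counterparts stay in the control arm leaves groups that randomisation did not create.

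The child-removal rule covers both arms but is discretionary and can be applied late. A report from an intervention nurse also tells the investigator which arm the family is in, and the program might itself affect whether removal happens.

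Section 10.2 promises that none of this alters the comparison. As written, the protocol supports two different analysis sets. Women excluded and no longer assessed cannot be recovered at the analysis stage.

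**Working it through.** **1. Timing of the need-based rule.** Under Sections 6.1, 7 and 8 a researcher carries out screening, consent, baseline assessment and allocation. No nurse takes part before randomisation. The program nurse receives a woman's details afterwards. Control women are not offered the program, and their first listed nurse contact is postnatal, whereas randomisation takes place in pregnancy. So whichever nurse is meant, her opinion most plausibly comes after allocation. If the program nurse is meant, it comes from one arm only.

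**2. Timing of the child-removal rule.** Participants are pregnant when randomised, so removal of the study child comes after allocation. Section 6.2 says women are randomised only if no exclusion criterion is met; that check cannot cover a later event. The intervention arm has two reporting routes (nurse or phone call) and the control arm one (phone call).

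**3. The plan's own power figure.** Inputs from Section 10.1: 400 per arm, 60% retention, 0.315 SD, ICC 0.02, cluster size 29, 80% power. Alpha is not stated; 0.05 two-sided is assumed.

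- Design effect = 1 + (29 − 1) × 0.02 = 1.56
- Retained per arm = 400 × 0.60 = 240
- SE of the difference = √(2 × 1.56 / 240) = 0.114 SD
- Power = Φ(0.315 / 0.114 − 1.96) = 78.9%

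This agrees with the stated 80% to within about one point. The concern does not depend on it; it supplies the scale.

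**4. Size of a one-arm exclusion.** Let f be the share of one arm excluded and d the difference, in SD, between their mean outcome and that whole arm's mean. The arm difference then shifts by f × d / (1 − f). The protocol gives neither quantity, so the ranges below are assumed. Shift in SD:

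| f | d = 0.2 | d = 0.5 | d = 0.8 |
|---|---|---|---|
| 2% | 0.004 | 0.010 | 0.016 |
| 5% | 0.011 | 0.026 | 0.042 |
| 10% | 0.022 | 0.056 | 0.089 |
| 15% | 0.035 | 0.088 | 0.141 |

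Worked example: 0.10 × 0.5 / 0.90 = 0.056 SD, and 0.056 / 0.315 = 18% of the target. Across the table the shift is 1% to 45% of the target.

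**5. Effect on error rates.** In the worked example the intervention arm has 240 × 0.90 = 216 women, so SE = √(1.56/240 + 1.56/216) = 0.117. With no true effect, two-sided type I error is Φ(−1.96 + 0.056/0.117) + Φ(−1.96 − 0.056/0.117) = 7.6%. Across the table it runs from 5.0% to 22%. If the shift works against a true effect of 0.315 SD, power in the example falls from 78.9% to 60.1%.

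**6. The power rationale.** Suppose the effect is unchanged and 5% or 10% of retained women are removed equally from both arms. Power then falls from 78.9% to 76.8% or 74.6%. Exclusion could raise power only if those removed would have benefited less, and the gain would then apply to a different population.

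**The case against.** The need-based rule is loosely drafted and discretionary. It follows a check confined to the first 20 women enrolled, and it does not reappear in the exclusion list of Section 6.2.2 or the withdrawal list of Section 6.6.1. Control women also have maternal and child health nurses, as Section 10.1 notes. A reader might infer that the protocol states the rule operates only in the intervention arm. It does not; that is a strong inference from when program nurses are assigned.

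Three other stronger readings should be resisted.

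- **That Section 6.6.1 contradicts Section 10.2.** It concerns withdrawal from treatment and follow-up, not from the analysis set. Section 10.2 covers women who withdraw, Section 6.6.2 asks those leaving the program to continue assessments, and Section 10.3 plans complete-case and imputed analyses. Nor does it let the team withdraw anyone at will: the relevant item describes a participant who requires early discontinuation.
- **That child removals would be found mainly through program nurses.** Section 6.2.2 names two routes and gives no proportions. Research contacts follow the same schedule in both arms, and the 24-month home visit could reveal removal in either. Only the extra route is documented.
- **That only withdrawal of consent should end follow-up.** Such a rule would reach pregnancy loss, neonatal death and adverse events, whose handling is not at issue here.

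The magnitudes are also assumed. The formula supposes that every excluded woman would otherwise have supplied an outcome. Section 6.2 expects less vulnerable women to drop out anyway, and Section 10.1 plans for 60% retention, so the added shift could be smaller.

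These points limit the claim. They do not remove the conflict between the two exclusion rules and Section 10.2.

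**Conclusion.** The concern holds for the two exclusion rules. The need-based rule most plausibly acts after allocation, mainly or only in the intervention arm, and selects on vulnerability. The child-removal rule acts after allocation in both arms, with case-by-case decisions, no stated blinding of those deciding, and an additional reporting route in one arm. Both are inconsistent with an as-randomised comparison.

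The direction of bias is not certain. Losing less vulnerable women from the intervention arm would tend to work against the program; losing more removed-child families from that arm would tend to favour it. The size cannot be estimated from the protocol. Under the assumed ranges it runs from negligible to nearly half the target difference. The case for change rests on the inconsistency and on the irrecoverable loss of data, not on any single figure.

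**What to change.** Reconcile Sections 6.2 and 6.2.2 with Section 10.2.

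- **Section 6.2:** apply any need-based or refined eligibility criteria only to women not yet randomised. After randomisation, record perceived need as a process measure.
- **Section 6.2.2:** do not use child removal to take a randomised family out of the analysis set. Treat 24-month outcomes that cannot be obtained as missing, and report removals by arm.
- **Section 6.6.1:** add only that withdrawal initiated by the team does not remove a woman from the intention-to-treat set. Leave unchanged when the program stops and how pregnancy loss, neonatal death and adverse events are handled.

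The cost is a wording amendment. The planned 400 per arm need not change. Some low-need or removed-child families stay in, which may dilute the estimate slightly, and some of their outcomes will be missing.
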